### Methods for additional analyses, e.g. to handle missing data (e.g. subgroup analyses) {20b}{20c}

Patients lost to follow-up during treatment will have an unfavourable treatment outcome. In case data are missing for an independent categorical variable, the missing indicator method will be used, and a category “missing” will be added.

### Plans to give access to the full protocol, participant level-data and statistical code {31c}

Once completed, de-identified trial data will be shared upon request and approval by the National Tuberculosis Program of Niger and Damien Foundation Niger.

## Oversight and monitoring

### Composition of the coordinating centre, trial steering committee, data monitoring committee {5d}{21a}

The trial is sponsored by DF. The trial is implemented by the NTP through the RR-TB National Committee and DF. ITM provides DST and research expertise. The treatment monitoring group consists of the principal investigator (from DF), the technical RR-TB referent from DF, the focal point of the Niger RR-TB National Committee, and a co-investigator from ITM. The treatment monitoring group will meet to discuss the results of the interim analysis and decide whether enrolment should continue, or not (see the interim analysis).

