### Outcomes {12}

Primary endpoint, as a measure of safety: any severe (grade 3–5) AE, with onset of symptoms before the end of treatment, and with the maximum grade measured up to 6 months after the end of treatment.

Secondary endpoints:As a measure of effectiveness: treatment outcome, with relapse-free success (cure or treatment completion without proof of relapse during 12 months of active post-treatment follow-up) as favourable outcome and treatment failure, relapse, lost to follow-up, and death as an unfavourable outcome.As a measure of adherence to the regimen: proportion of daily doses taken.

The definitions used to grade AE are based on French National Agency for Research on AIDS and hepatitis (ANRS) [19].

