### Sample size {14}

A total of 230 patients will be included prospectively to compare treatment arms (115 patients for each) in order to be able to identify a correlation between the treatment arms and the occurrence of any grade 3–5 AE, assuming that the “hazard ratio” for developing a grade 3-5 AE is 3.2 times higher among patients in the experimental treatment arm (WHO all-oral regimen) compared to the control arm (STR that contains either a SLID or LZD; 5% vs 15%; with power 0.8, alpha 0.05).

Justification of assumptions :Of the 153 patients already treated according to the Niger RR-TB treatment strategy, with LZD replacing the SLID in the STR in case of ototoxicity and with monthly audiometry, 6 (3.9%) had an AE of degree 3–5 [15]. For the calculation of the sample size, a “conservative” estimate of 5% was used.Of the 33 patients treated with linezolid instead of the SLID in case of ototoxicity, 6 (18.2%) had grade 3–5 AE [15]. A “conservative” estimate of 15% was used to calculate the sample size.

In addition to the prospective treatment arms, a retrospective cohort of 255 patients enrolled on treatment between 2017 and April 2021 will be used during an interim analysis (see interim analysis), if characteristics known to affect the treatment outcome of the retrospective cohort are not significantly different from the prospective arms, and in case the proportion with a grade 3-5 adverse event is not significantly different between the retrospective cohort and those prospectively treated using the Niger RR-TB treatment strategy (SLID-containing regimen, with LZD replacing the SLID in case of ototoxicity).

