### Data management {19}

For this pragmatic trial, we rely on routinely used data sources, such as the laboratory register, RR-TB treatment register, and the patient’s RR-TB treatment card. Data are imputed in Excel sheets, used for routine reporting since 2008 [8]. All source documents, as well as the consent forms, are archived at the RR-TB clinics. Routinely conducted quarterly supervision visits ensure data completeness. These visits are performed by the national RR-TB focal point, part of the National RR-TB Committee.

Data from these sources will be encoded in a national database in Excel (already is in place), and updated regularly by the research assistants, supervised by the principal investigator.

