### Interim analyses {21b}

As soon as the safety data for 80 prospectively included patients are available, an intermediate analysis will be carried out to evaluate whether a significant association exists between the treatment arm (experimental vs control) and the occurrence of the safety endpoint (any grade 3–5 AE), using Cox regression, as described above for the primary analysis.

As the Niger approach to RR-TB treatment (SLID-containing STR with LZD replacing the SLID in case of audiometry abnormalities) was already successfully used and as data were collected rigorously, using the same procedures that will be applied in the trial, interim analyses will also include the retrospective cohort if the characteristics of the cohort are not significantly different from the prospective cohort with both treatment arms (the chi-square test will be used to compare HIV status, bacillary load, extent of TB disease and body mass index), and in case the proportion with a grade 3–5 adverse event is not significantly different between the retrospective cohort and those prospectively treated using the Niger RR-TB treatment strategy. To assess whether data from the retrospective cohort can be used, besides age and gender, characteristics known to predict safety (BMI, co-morbidities) and effectiveness (baseline bacillary load, baseline resistance profile) will be compared between the retrospective and prospective cohorts.

If the interim analysis shows a significant difference between the experimental arm and the control arm in terms of the primary endpoint before the total sample size is reached, study enrolment will be discontinued.

In case enrolment continued after the first interim analysis, and as soon as safety data are available for 160 patients enrolled in the trial, a second interim analysis will be conducted, using the same approach as used during the first interim analysis.

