### Frequency and plans for auditing trial conduct {23}

Regular data review and data monitoring and cleaning for quality control is performed quarterly in accordance with GCP guidance requirements by the principal investigator and national RR-TB focal point.

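### It is unclear whether the interim stopping criterion binds the treatment monitoring group, and two of the group's members see by-arm results while supervising and cleaning the safety data

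*Protocol article*

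**What the plan says.** **Interim analyses {21b}.** Cox regression on the primary endpoint is run when safety data are available for 80 patients and, if enrolment goes on, for 160. If the difference between arms is significant "before the total sample size is reached, study enrolment will be discontinued". The Discussion repeats this purpose: the looks exist to end enrolment early if severe events are significantly more frequent in one arm.

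**Composition of the coordinating centre {5d}{21a}.** "The treatment monitoring group will meet to discuss the results of the interim analysis and decide whether enrolment should continue, or not". A parenthesis then points to the interim section. The members are the principal investigator and a technical referent, both from the sponsor, the focal point of the national committee, and a co-investigator from the partner institute.

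**Data roles.** Under Data management {19} the national database is "updated regularly by the research assistants, supervised by the principal investigator", and the focal point makes the quarterly supervision visits. Under auditing {23}, data review, monitoring and cleaning are done quarterly "by the principal investigator and national RR-TB focal point".

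**Endpoint.** Outcomes {12} defines it as "any severe (grade 3–5) AE, with onset of symptoms before the end of treatment". It carries no condition on cause. The outcome-assessment section {18a} gives the grading to the investigator who treats the patient.

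**Openness.** Clinicians, patients, researcher and statistician are all unblinded {17a}. The Dissemination plans {31a} allow interim results to appear in abstracts or manuscripts before the primary results are published.

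**The concern.** There are two linked problems.

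The first is the status of the criterion. One section describes a consequence and the other a decision. The probability of a false-positive conclusion, and what an early stop means, depend on whether a significant look always ends enrolment or whether a committee may continue. The reverse is open too: nothing in the oversight wording prevents a stop without a significant result.

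The second is who learns the result. The trial is open-label, and the Trial design section declares the hypothesis that the control strategy is safer. A grade 3 event counts towards the endpoint and a grade 2 event does not, and Table 2 separates them partly by degree of activity limitation, which needs judgement. People who know that one arm is ahead may, without intending to, query or check that arm's records differently. If the looks do not stop the trial, this applies to all data gathered after them.

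**Working it through.** **1. The plan's own figure, which sets the timing of the looks.** Sample size {14}: "A total of 230 patients will be included prospectively to compare treatment arms (115 patients for each"), a hazard that "is 3.2 times higher among patients in the experimental treatment arm", and "5% vs 15%; with power 0.8, alpha 0.05". Sidedness is not stated; two-sided is taken here. With the Schoenfeld formula and 1:1 allocation:

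events = (1.960 + 0.842)² / (0.25 × (ln 3.2)²) = 7.85 / (0.25 × 1.353) = 23.2

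Mean event proportion = (0.05 + 0.15) / 2 = 0.10, so N = 23.2 / 0.10 = 232. The stated 230 reproduces within 1%. The looks fall at 80/230 = 0.35 and 160/230 = 0.70 of the planned patients.

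**2. The two stopping passages side by side.**

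| Section | Trigger | What follows |
|---|---|---|
| Interim analyses {21b} | significant difference on the primary endpoint | enrolment ends; no discretion mentioned |
| Discussion | endpoint significantly more frequent in one arm | enrolment ends early |
| Oversight {5d}{21a} | group meets on the interim result | group decides; refers back to {21b} |

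The cross-reference ties the third row to the first but does not say that the group is bound by it. Both readings remain possible.

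**3. Whether the difference matters: an illustration.** Assumptions:

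- no true difference between arms;
- two-sided 0.05, unadjusted, at both looks and at the end;
- information proportional to patients;
- prospective patients only;
- a significant look that is overridden leaves the later tests to decide, with the override chance applied separately at each look.

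Normal-theory simulation with 2,000,000 runs:

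| Chance that the group overrides a significant look | Overall type I error |
|---|---|
| 0% (criterion binds) | 10.6% |
| 25% | 9.3% |
| 50% | 8% |
| 75% | 6.5% |
| 100% (looks never stop the trial) | 5.0% |

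The table shows only that the operating characteristics differ between the two readings. It does not recommend overriding, and the choice of an interim significance level is a separate question.

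**4. Who holds which role.**

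| Role | Principal investigator | National focal point | Sponsor's technical referent | Partner-institute co-investigator |
|---|---|---|---|---|
| Sees and acts on interim results {5d}{21a} | yes | yes | yes | yes |
| Supervises database {19} | yes | – | – | – |
| Supervision visits {19} | – | yes | – | – |
| Reviews and cleans data {23} | yes | yes | – | – |

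A dash means that the article assigns no such role. Two of the four members combine interim knowledge with data handling, and two do not.

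**The case against.** **The cross-reference settles it.** One section gives the rule and the other names the body that carries it out, with an explicit pointer between them. Nothing says that the group may override a significant result. This is a fair reading and may be the intended one. It rules out calling the passages a plain contradiction. What stands is that a choice between continuing and not continuing is never said to be bound by the criterion.

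**Causality assessment.** A reader might infer that interim knowledge biases the primary endpoint through causality judgements. The document does not support that. The endpoint counts any grade 3–5 event whatever its cause. Causality enters only the additional Cox model comparing injectable and linezolid exposure {20a}. The article gives causality to the physician in charge of the study; that this is the principal investigator is an inference from one row of Table 3. Those who set the grades, the treating investigators, are not listed as members of the group either. The route that remains is supervision, review and cleaning, and the document does not show that this would alter recorded grades.

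**How often the sections would conflict.** A reader might take the chance of a significant look under 5% versus 15% as the frequency of conflict. It is not. It measures significance, and becomes conflict only if the group is assumed free to override. It also depends on the test: with 40 and 80 per arm and an assumed 0.05, it is about 62% by the second look with chi-square and about 50% with Fisher's exact test, whereas the plan names Cox regression and may add a retrospective cohort of 255.

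**Withholding tables achieves little.** The trial is open-label, and someone who supervises the database can tabulate events by arm. That is largely true and limits the gain. The national committee also reviews safety data quarterly {22}, but this is no independent check, because the focal point belongs to it.

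**Conclusion.** The point holds in a limited form. The article leaves it unclear whether the interim criterion binds the treatment monitoring group. It also gives by-arm interim results to two people who go on to supervise and clean the same open-label safety data.

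For the first part, the size is the range from about 10.6% to about 5.0% in type I error, conditional on the assumed 0.05 per look and information proportional to patients. For the second part no size can be given: the document has no figure from which to estimate a change in recorded grades, and none is claimed. The finding rests on what the article states about roles and decisions, and not on anything that a full protocol or analysis plan might add. It merits correction because the wording is easily repaired and interim looks are part of the design; it does not show that the trial's results would be wrong.

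**What to change.** 1. Align Interim analyses {21b} and the oversight section {5d}{21a}: state in one of them, and refer to it from the other, that the group applies the interim criterion and records its reasons in writing for any departure. The significance level that goes into the criterion should be settled separately.
2. Have the statistician prepare the by-arm interim tables and show them only to group members with no data supervision or cleaning role. On the article's list these are the sponsor's technical referent and the partner-institute co-investigator, provided that neither has such a role in practice. The principal investigator and the focal point are told only whether to continue or stop while enrolment and follow-up go on.
3. Amend the Dissemination plans {31a} so that interim results by arm are not released while the trial continues.

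The cost is wording in three sections, with no extra patients, analyses or staff. The downside is that the principal investigator and the focal point lose the by-arm interim tables. The protection is partial, since treatment is open-label and the principal investigator supervises the database.

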### Adverse event reporting and harms {22}

All AEs that occur during the study are documented and followed until resolution or stabilisation. All AE will be recorded in the patient’s file and in a database by type, degree and month of occurrence. All SAE (grade 4–5 AE or AE requiring hospitalisation) deemed related to one or more investigational product(s) and considered unexpected with the use of such products are reported to National Regulatory Authorities. All other severe AEs are reported in an annual safety report. In addition, safety data is reviewed quarterly by the RR-TB National Committee, the members of which have expertise in clinical trials, RR-TB, pharmacology. Line listings of all reported serious AE’s will be sent on a yearly basis to the National Pharmacovigilance Unit and ethics review bodies.

### Frequency and plans for auditing trial conduct {23}

Regular data review and data monitoring and cleaning for quality control is performed quarterly in accordance with GCP guidance requirements by the principal investigator and national RR-TB focal point.

### Plans for communicating important protocol amendments to relevant parties (e.g. trial participants, ethical committees) {25}

In case the procedures would have to change, an amendment will be developed and submitted to the relevant ethics review bodies.

### Dissemination plans {31a}

The results will be communicated through abstract presentations at scientific conferences and publications in peer-reviewed journals. The results of the intermediate analysis can be used for abstracts or manuscripts, prior to the publication of the results of the primary analysis.

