## Data collection and management

### Plans for assessment and collection of outcomes {18a}

Safety: Patients will be screened monthly by a person trained in the diagnosis and management of AE.

During the inclusion visit, pathologies associated with a high risk of adverse effects such as diabetes, kidney and liver failure, malnutrition, HIV infection, alcohol and drug abuse, etc. should be identified and recorded. The underlying causes of adverse effects will be identified and treated.

AE are classified according to their severity using ARNS scale (Table 2) and noted in the patient’s file.

**Table 2 Tab2:** Severity rating of adverse effects

Degree	Description
Degree 1: Slight abnormality	Mild or transient discomfort, without limitation of usual daily activity; does not require medical intervention or corrective treatment.
Grade 2: Moderate abnormality	Partial limitation of usual daily activity; medical intervention or corrective treatment required. No need to interrupt treatment.
Grade 3: Severe abnormality	Limitation of usual daily activity; requires medical intervention and corrective treatment, possible hospitalisation. It may be necessary to stop the responsible medication temporarily until the symptoms disappear.
Grade 4: Life threatening or permanent injury	Very limited activity; requiring medical intervention and corrective treatment, almost always in a hospital environment. It may be necessary to stop the responsible drug permanently.
Grade 5: Death	

Grade 1 adverse events will only be recorded in the patient's file without further action; those of grade 2 often require a medical intervention with auxiliary drugs

Any grade 3–5 AE are classified as severe AE

All AE will be reported in the patient treatment card. When an AE occurs, the investigator responsible for the care of the patient will first assess and grade the event. If it is graded 4–5, or if other serious AE (SAE) criteria (such as hospitalisation) apply, then a “severe AE form” will be completed and sent to the principal investigator and the relevant pharmacovigilance authority (Fig.1).

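### The dissemination plan lets by-arm interim safety results be published without requiring that enrolment has closed, which could add to expectation bias in an open-label trial

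*Protocol article*

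**What the plan says.** Dissemination plans {31a} gives a permission with no condition attached: "The results of the intermediate analysis can be used for abstracts or manuscripts, prior to the publication of the results of the primary analysis". Nothing there, or elsewhere in the protocol article, ties early publication to closed enrolment, completed follow-up or completed grading of adverse events.

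Interim analyses {21b} defines what would be published. "As soon as the safety data for 80 prospectively included patients are available, an intermediate analysis will be carried out", with the aim to "evaluate whether a significant association exists between the treatment arm (experimental vs control) and the occurrence of the safety endpoint". This is a comparison of the two arms on the primary endpoint. If the difference is significant, "study enrolment will be discontinued". Otherwise recruitment goes on, and a second look follows: "In case enrolment continued after the first interim analysis, and as soon as safety data are available for 160 patients enrolled in the trial".

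The section on the composition of committees {5d}{21a} says who handles the results: "The treatment monitoring group will meet to discuss the results of the interim analysis and decide whether enrolment should continue, or not". That group includes the principal investigator and a co-investigator.

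On outcome assessment {18a}, "the investigator responsible for the care of the patient will first assess and grade the event". Under the blinding items, clinicians and patients know the regimen, as do the researcher and the statistician. Under Sequence generation {16a}, one coin toss fixed the arm for all odd and all even calendar months.

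**The concern.** Comparative interim results on a primary endpoint are normally kept from the people who recruit patients and assess that endpoint until both tasks are finished. Here the protocol expressly allows the results to become public earlier, in a trial with little to absorb the effect.

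Two routes are open.

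- **Grading.** Table 2 separates grade 2 from grade 3 largely by how far daily activity is limited, which leaves room for judgement, and that boundary decides the primary endpoint. An investigator who has read that one arm is doing worse may grade borderline events in that arm higher.
- **Consent.** Clinicians and patients can tell the arm from the month of diagnosis before consent is given. A published trend could influence who agrees to take part in odd or even months.

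The Discussion accepts that clinicians may act on their view of the regimens: it gives this as the reason for allocating by date of diagnosis instead of date of treatment start.

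The issue is separate from the significance level used at the interim looks. Correcting that level would not stop the results from circulating.

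**Working it through.** **1. Does the text allow publication during recruitment?** Three statements have to be read together.

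- {31a}: interim results may appear before the primary publication, with no further condition.
- {21b}: the interim result is a between-arm comparison of the primary endpoint.
- {21b}: enrolment stops only if that comparison is significant; a second look is planned for the case in which it is not.

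A non-significant first interim therefore leaves a trial that is still recruiting and holds a comparative result it may publish. This follows from the sections jointly; no single sentence states it.

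**2. The denominator.** Sample size {14} gives 230 patients for a hazard ratio of 3.2, 5% vs 15%, power 0.8 and alpha 0.05. Schoenfeld's formula, two-sided with 1:1 allocation:

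- events = (1.960 + 0.842)² / (0.25 × (ln 3.2)²) = 7.849 / 0.3382 = 23.2
- patients = 23.2 / 0.10 (mean of 5% and 15%) = 232, against 230 stated

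The figure reproduces closely. Nothing in this point changes it.

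**3. Patients outside each interim dataset.**

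- First interim: 230 − 80 = 150 (150/230 = 65%)
- Second interim: 230 − 160 = 70 (70/230 = 30%)

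These are upper bounds for the number still to enrol, because the trigger is availability of safety data and not enrolment of the 80th or 160th patient.

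**4. Patients still to enrol.** Trial status gives 36 months of recruitment. Assuming uniform accrual, 230/36 = 6.39 per month, so the 80th patient enters at 80/6.39 = month 12.5 and the 160th at 160/6.39 = month 25.0. The protocol does not say how long after enrolment safety data count as available, so the lag is an assumption. The range is 0 (extreme), 9 to 11 months (treatment duration), and 15 to 17 months (treatment plus the 6 months allowed for the maximum grade under Outcomes {12}). Patients enrolled by the interim = 6.39 × interim month, capped at 230.

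| Lag (months) | First interim, month | Enrolled | Still to enrol | Second interim, month | Still to enrol |
|---|---|---|---|---|---|
| 0 | 12.5 | 80 | 150 | 25.0 | 70 |
| 9 | 21.5 | 138 | 92 | 34.0 | 12 |
| 11 | 23.5 | 150 | 80 | 36.0 | 0 |
| 15 | 27.5 | 176 | 54 | 40.0 | 0 |
| 17 | 29.5 | 189 | 41 | 42.0 | 0 |

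The first interim falls within recruitment across the whole range. The second may fall within it or after it. Time from analysis to publication would lower the numbers further.

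**5. Grading exposure.** This is not limited to patients still to enrol. Anyone on treatment or in the following 6 months can still have a grade set, so the exposure lasts 9 + 6 = 15 to 11 + 6 = 17 months after the last enrolment. How many events would be graded after publication cannot be derived from the protocol.

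**The case against.** Much of the expectation exists without any publication. The protocol states as its hypothesis that the all-oral regimen is less safe, and it reports earlier grade 3–5 rates of 3.9% under the Niger strategy and 18.2% among those switched to linezolid. Treatment is open-label, and the RR-TB National Committee reviews safety data quarterly. This stands: publication would reinforce an existing expectation, and its own share cannot be separated. But staff who know their own patients' arms do not thereby know the trial-wide comparison across four units, and publication would extend that knowledge from a small group to every grader and patient.

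Several monitored toxicities rest on laboratory or instrument results such as blood counts, creatinine, liver enzymes, audiometry and ECG, which leaves less room for judgement. The allocation month is the one printed on the Xpert result, and the laboratory staff do not know which regimen belongs to it, so redirecting patients between arms is hard. Both points stand. They narrow the problem to the more subjective gradings and to consent.

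Timely information for guidelines is a declared aim, and holding back a significant safety finding until the last patient's window closes could mean a wait of 15 to 17 months after the last enrolment. This also stands, and the fix has to allow for it.

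Three stronger readings are tempting and lack support.

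- A reader might infer that the sponsor plans to publish during enrolment. The text only fails to exclude it.
- A reader might take all 150 patients as still to be recruited at the first interim. That is the upper bound.
- A reader might put a percentage-point figure on the distortion and set it against the planned 10-point difference. That needs the share of patients whose worst grade is 2 and the rate of upgrading by arm; the protocol gives neither.

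**Conclusion.** The point holds in a limited form. The protocol permits by-arm interim results on its primary safety endpoint to be published before the primary analysis, does not restrict this to the period after enrolment has closed, and foresees enrolment continuing after non-significant looks at 80 and 160 patients. With open-label treatment, grading by the treating investigator and an arm known from the calendar month, publication during recruitment could add to expectation bias in grading and consent.

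It is a risk of unknown size. What can be bounded is the recruitment still exposed: about 41 to 150 of 230 patients at the first interim and 0 to 70 at the second, given uniform accrual over 36 months and a data lag of 0 to 17 months. If an interim is significant and enrolment stops, the consent route disappears and only the grading of patients still under observation remains open.

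Because the protocol itself states the permission, this is not a detail left to an analysis plan.

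**What to change.** Amend Dissemination plans {31a} to distinguish two cases.

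- **Enrolment continues after an interim.** By-arm results stay within the treatment monitoring group, and the sites hear only 'continue'. No by-arm interim result is published or presented until enrolment has closed and grading of the primary endpoint is complete.
- **Enrolment is stopped for a significant safety difference.** Results may be released promptly. Gradings made after release, in patients still in the endpoint window, are reported separately or examined in a sensitivity analysis.

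The safety reporting to authorities and ethics bodies under {22} stays as it is, and the sample size does not change. The cost is a short protocol amendment and, when the trial continues, a delayed interim abstract.

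The amendment does not remove all exposure. The treatment monitoring group includes the principal investigator and the national RR-TB focal point, who also carry out the quarterly data review and cleaning under {23}. It only keeps the comparison from spreading to all site staff and patients.
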